### 2.7. The Outcomes

The primary outcome of this study is the occurrence of SUI at the 6th week postpartum, which will be diagnosed based on urinary leakage when abdominal pressure increases or positive stress test. A positive result of the stress test is defined as involuntarily urinary leakage during Valsalva or coughing in the lithotomy position.

The secondary outcomes include: (1) the occurrence of SUI at the 12th month postpartum; (2) the PFM strength at the 6th week and 12th month postpartum, which will be measured with the MOS and pelvic floor electrophysiological test.

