## Abstract

Background: As the effectiveness on stress urinary incontinence (SUI) prevention of pelvic floor muscle training (PFMT) for pregnant women has been inconclusive, we are planning to conduct a trial to evaluate a video program designed for prevention of SUI developed through combining PFMT with global postural reeducation (GPR). Methods: As a randomized controlled trial, eligible participants will be randomized (1:1) into an exercise group and a control group to perform PFMT regularly following video guidance or with no intervention, respectively. The experimental stage will be from the 16th gestation week (GW) to the 12th month postpartum, with eight appointments at the 16th, 28th, 37th GW, delivery, the 6th week and the 3rd, 6th, and 12th month postpartum. Data will be collected regarding urinary leakage symptoms, the stress test, the modified Oxford Scale, pelvic floor ultrasound, perineal laceration classification at delivery, neonatal Apgar score, and questionnaires (PISQ-12, ICIQ-UI SF, I-QOL, OABSS). The primary outcome is the occurrence of the symptomatic SUI and positive stress test at the 6th week postpartum. Discussion: This protocol is anticipated to evaluate the efficacy of the intervention via video app for the design of a future randomized control trial (RCT). Trial registration: The trial has been registered at Chinese Clinical Trial Registry (registration number: ChiCTR2000029618).

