### 2.8. Sample Size

The sample size was calculated using PASS 2019 software. Qi et al. [2] reported 25.7% of the 8-week postpartum SUI occurrence. Because there is lack of SUI occurrence in 6-week postpartum to refer to, we hypothesize the 6-week postpartum SUI occurrence is about 25.7% and the occurrence of SUI in EG will dropped to 15% after the trial. Based on 10.7% of occurrence difference between two groups at 6-weeks postpartum, a total of 586 participants (293 per group) is required to provide 90% statistic power at the two-sided significance level of 0.05. In considering 20% of the possible dropout, we decided to recruit 734 participants (367 subjects in each group) for the trial.

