### 2.9. Statistical Analysis

Statistical analysis will be conducted using SPSS version 23.0 and the assumed significance level was 5%. Categorical variables will be described as numbers and percentages. If continuous variables followed a normal distribution, data will be represented as means ± standard deviations (SDs). Otherwise, medians (P25, P75) will be calculated when continuous variables do not follow a normal distribution. For the primary outcome, we will compare the occurrence of SUI at 6-week postpartum between EG and CG by chi-square test or Fisher’s exact test as appropriate. For secondary outcomes, the counting data will be analyzed by logistic regression and the quantitative data will be compared by linear regression as appropriate.

Statistical analyses will be conducted on an intention-to-treat (ITT) basis by the statistician at Peking University Clinical Research Institute. Data analyses of EG will also include those regarding the participants’ adherence to the protocol with at least 80% participation to be the indicator of task achieved.

The outcome analysis will be conducted with multiple imputations to take missing values into account. The statisticians will perform sensitivity analyses of the outcome first by imputing missing values as failures and then by using complete cases.

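### The abstract defines the primary outcome as symptoms AND a positive stress test, section 2.7 as symptoms OR a positive stress test, and nothing in the protocol says which prevails

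*Protocol article*

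**What the plan says.** The primary outcome is described in two places in the protocol article, both current text.

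- Abstract: "The primary outcome is the occurrence of the symptomatic SUI and positive stress test at the 6th week postpartum".
- Section 2.7 (The Outcomes): SUI at the 6th week, "which will be diagnosed based on urinary leakage when abdominal pressure increases or positive stress test". The same section defines the test: "A positive result of the stress test is defined as involuntarily urinary leakage during Valsalva or coughing in the lithotomy position".

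The other relevant sections do not restate the rule.

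- Section 2.8 (Sample Size): "we hypothesize the 6-week postpartum SUI occurrence is about 25.7" per cent, and "the occurrence of SUI in EG will dropped to 15% after the trial". It cites an 8-week postpartum rate as its source and does not say how cases were defined there.
- Section 2.9 (Statistical Analysis): "we will compare the occurrence of SUI at 6-week postpartum between EG and CG by chi-square test or Fisher’s exact test as appropriate".
- Table 1: leakage symptoms and the stress test are both mandatory at the 6th week and at the 12th month.

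The first secondary outcome, SUI at 12 months, uses the same term.

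**The concern.** The two sentences describe different endpoints. The AND rule counts a subset of the women counted by the OR rule, and the gap is every woman with exactly one component. Because both components are collected from everyone at week 6, both endpoints can be computed from the same data, and the plan has one primary test to apply. If the two rules gave different results, the protocol as written could be cited in support of either.

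The rules also differ in what they measure. Section 2.4 says that participants cannot be blinded while evaluators are masked. Under OR, a participant's own report is enough to make a case. Under AND, a masked examination must also be positive. The choice therefore affects exposure to reporting bias as well as the event rate.

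Finally, the planning rates of 25.7% and 15% are not tied to either rule, so the reader cannot tell which endpoint the stated power belongs to.

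**Working it through.** **Step 1. The two rules side by side (week 6).**

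| Leakage symptoms | Stress test | Case under abstract (AND) | Case under section 2.7 (OR) |
|---|---|---|---|
| yes | positive | yes | yes |
| yes | negative | no | yes |
| no | positive | no | yes |
| no | negative | no | no |

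The rules disagree in the two middle rows. The AND rate can never exceed the OR rate in the same women. The protocol gives no figure for how many women fall in the middle rows.

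**Step 2. Does the stated sample size reproduce?** Inputs from section 2.8: control 0.257, exercise 0.15, two-sided alpha 0.05, power 90%, 20% dropout. Allocation is 1:1 (section 2.4).

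- Unpooled normal approximation: n = (1.960 + 1.282)² × (0.257 × 0.743 + 0.15 × 0.85) / 0.107² = 10.507 × 0.31845 / 0.011449 = 292.3, so 293 per group. This matches the protocol.
- Pooled variance gives 296 per group. Pooled power at 293 per group is 89.8%.
- Dropout: 293 / 0.80 = 366.25, so 367 per group and 734 in total. This also matches.

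The arithmetic is not at fault.

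**Step 3. What the definition could do to power (illustration only).** These assumptions are not in the documents: 25.7% is a symptom-based rate; the stress test is positive in 30–70% of symptomatic women; it is positive in 3–10% of asymptomatic women. Pooled test, 293 per group.

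Control rates:
- AND: 0.257 × 0.30, 0.50, 0.70 = 7.7%, 12.9%, 18.0%.
- OR: 0.257 + 0.743 × 0.03, 0.05, 0.10 = 27.9%, 29.4%, 33.1%.

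| Effect assumption | AND power | OR power |
|---|---|---|
| Constant risk ratio 0.15/0.257 = 0.584 | 37%, 57%, 74% | 93%, 94%, 97% |
| Constant 10.7-point difference | impossible at 7.7%; above 97% at 12.9% and 18.0% | 87%, 86%, 83% |
| Same positive-test rate in asymptomatic women of both arms (exercise OR rate 0.15 + 0.85 × 0.03, 0.05, 0.10 = 17.6%, 19.3%, 23.5%) | not applied | 85%, 82%, 74% |

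Under OR, power lies above 90% in the first row and below it in the other two. Under AND, it falls well below 90% in the first row and rises above it in the second, where the difference is possible at all. The direction depends on an effect assumption that the protocol does not settle, so no row can be quoted as the trial's power.

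**The case against.** The strongest reply is that section 2.7 governs. It is the only place that says how SUI is diagnosed and what a positive test is, and sections 2.8 and 2.9 then use the term it defines. An abstract is a summary, and its conjunction may simply list the two things assessed. Much of this stands: section 2.7 is the fuller text, and nothing shows that a second endpoint was deliberately planned. It does not remove the conflict. The abstract names a specific combination rather than just SUI, no sentence gives an order of precedence, and if the abstract meant two separate outcomes, that too would differ from the single composite in section 2.7. Nor is this a detail left to an analysis plan, since the article itself states the primary outcome in two ways.

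A reader might go further and infer that the trial is underpowered. The documents do not support that. The loss to 37–74% arises only under the abstract's literal reading, with assumed component rates and a constant risk ratio. Section 2.8 frames its effect as an absolute difference ("Based on 10.7% of occurrence difference between two groups at 6-weeks postpartum"), and holding that constant reverses the direction under both rules.

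A reader might also infer that the endpoint should be whichever rule the 25.7% was measured with. That is the wrong way round, because a planning rate should be matched to the chosen endpoint. It may not even select a rule: a purely symptom-based rate corresponds to neither AND nor OR.

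**Conclusion.** The point holds. The protocol states its primary outcome in two incompatible ways, and the difference bears on the trial's single primary comparison and on the 12-month secondary outcome. It should be corrected before any 6-week outcome data are seen, because after that the choice of rule can no longer be shown to be independent of the results.

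The finding rests only on the two quoted sentences and on the absence of any text that ranks them. Its numerical size cannot be given, since the protocol reports no rates for women with one component alone. The claim of 90% power is correctly calculated for 25.7% against 15%. What is open is which case definition those two rates describe.

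**What to change.** 1. Choose one case definition and state it identically in the abstract and section 2.7, before any 6-week outcome data are seen. Section 2.7 is the fuller text and the natural place to anchor it.
2. Say that the same definition applies to SUI at the 12th month.
3. Name the other rule as a prespecified sensitivity analysis.
4. In section 2.8, state which case definition the 25.7% and 15% refer to. If it is not the chosen one, justify a control rate and an effect for the chosen one and restate the power.

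The cost is a change of wording in two or three places and, if step 4 requires it, one recalculated power figure. No new data are needed, since Table 1 already collects both components at both times.

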### 2.8. Sample Size

The sample size was calculated using PASS 2019 software. Qi et al. [2] reported 25.7% of the 8-week postpartum SUI occurrence. Because there is lack of SUI occurrence in 6-week postpartum to refer to, we hypothesize the 6-week postpartum SUI occurrence is about 25.7% and the occurrence of SUI in EG will dropped to 15% after the trial. Based on 10.7% of occurrence difference between two groups at 6-weeks postpartum, a total of 586 participants (293 per group) is required to provide 90% statistic power at the two-sided significance level of 0.05. In considering 20% of the possible dropout, we decided to recruit 734 participants (367 subjects in each group) for the trial.

### 2.9. Statistical Analysis

Statistical analysis will be conducted using SPSS version 23.0 and the assumed significance level was 5%. Categorical variables will be described as numbers and percentages. If continuous variables followed a normal distribution, data will be represented as means ± standard deviations (SDs). Otherwise, medians (P25, P75) will be calculated when continuous variables do not follow a normal distribution. For the primary outcome, we will compare the occurrence of SUI at 6-week postpartum between EG and CG by chi-square test or Fisher’s exact test as appropriate. For secondary outcomes, the counting data will be analyzed by logistic regression and the quantitative data will be compared by linear regression as appropriate.

Statistical analyses will be conducted on an intention-to-treat (ITT) basis by the statistician at Peking University Clinical Research Institute. Data analyses of EG will also include those regarding the participants’ adherence to the protocol with at least 80% participation to be the indicator of task achieved.

The outcome analysis will be conducted with multiple imputations to take missing values into account. The statisticians will perform sensitivity analyses of the outcome first by imputing missing values as failures and then by using complete cases.

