The twice-a-week GPR was originally programmed to be performed once following guidance of the app at home and once under face-to-face guidance of the physiotherapists. In consideration that it is not safe to organize face-to-face guidance in training rooms during COVID-19 pandemic and the need to regulate the postures and procedures and collect data to evaluate the compliance of the participants, we modified the protocol to organize video-trainings for EG participants to perform GPR under the living guidance of the physiotherapists on-video via Zoom meetings once a week. Four Zoom meetings will be scheduled for video training in each week, each focusing on one of the four exercise sets. An individual participant will be invited to visit one of the Zoom meeting to practice the exercises appropriate to her GW. Each video-meeting can be divided into several classes according to the number of participants, with each limited to 10 persons, so as to facilitate the physiotherapists to give enough care to each participant and to maximize the effectiveness. The site assistants will notify each participant the Zoom link specially for her in each week in advance, but keep her blind of the other Zoom meeting details to avoid protocol bias. The site assistant will also record the attendance of each participant in terms of the attendance time, the procedural and intensity compliance, and the adverse events, etc. Any participant absent at the scheduled class will be reminded to join the next class on the same exercise set so that she can “catch up” the scheduled one in the following Zoom meeting. The scheduled class will not be cancelled even with only one participant. The role of the physiotherapist is to guide participants in the class to accomplish the full exercise set and to regulate any inappropriate acts. To protect participants’ privacy, no video and audio records are taken and preserved during video-conference, which are fully informed to and consented by the participants.

Any pregnant participant experiencing abnormal symptoms (e.g., abdominal pain, vaginal bleeding, abnormal fetal movement, etc.) will contact the site assistant in each hospital, and the assistant will refer them to the obstetric department as soon as possible, followed by an assessment of whether they should continue the intervention or not. An anticipated adverse event report will be prepared and sent to the principal investigator (PI). 

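### Only the exercise arm is treated in live classes, but the primary test and the sample size treat all women as independent; the 5% level and 90% power hold only without class or physiotherapist effects

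*Protocol article*

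**What the plan says.** Section 2.4 randomises women individually, 1:1, from a list per centre in blocks of four. Under 2.5 the control group receives no intervention beyond routine care. The exercise group trains at home with the app and, once a week, does its postural session live on Zoom under a physiotherapist. On those sessions 2.5 says: "Each video-meeting can be divided into several classes according to the number of participants, with each limited to 10 persons". It adds: "The role of the physiotherapist is to guide participants in the class to accomplish the full exercise set and to regulate any inappropriate acts".

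Section 2.8 sizes the trial on the assumptions "we hypothesize the 6-week postpartum SUI occurrence is about 25.7" per cent and "the occurrence of SUI in EG will dropped to 15% after the trial", and concludes that "a total of 586 participants (293 per group) is required to provide 90% statistic power at the two-sided significance level of 0.05". The only inflation is for losses: "In considering 20% of the possible dropout", "we decided to recruit 734 participants (367 subjects in each group) for the trial".

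Section 2.9 fixes the primary analysis: "we will compare the occurrence of SUI at 6-week postpartum between EG and CG by chi-square test or Fisher’s exact test as appropriate". Neither 2.8 nor the primary test in 2.9 has a term for class or physiotherapist.

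**The concern.** This is an individually randomised trial with group treatment in one arm, known as a partially nested design. Exercise-group women who share a class or a physiotherapist may have correlated outcomes; controls do not share either.

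The protocol itself supplies a mechanism. Its Discussion holds that correct technique and compliance may determine whether training works. Section 2.5 makes the physiotherapist responsible for correcting technique, and caps class size so that each woman gets enough attention. If that teaching matters, its quality can differ between classes or physiotherapists.

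The chi-square and Fisher tests give the exercise-arm rate a binomial variance. With positive correlation within classes, that variance is too small. Two stated properties are then at stake: the 5% error rate of the planned test, and the 90% power of any test that estimates the variance correctly. Stratifying or adjusting by centre does not remove a class or physiotherapist effect.

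**Working it through.** **Inputs from the protocol.** Control rate 0.257, exercise rate 0.15, two-sided alpha 0.05, power 90%, 293 analysed per group, 20% dropout (all 2.8); class size at most 10, exercise arm only (2.5); 12 weeks of training (Discussion).

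**Assumed, not in the protocol.** The ICC, taken from 0.01 to 0.05. Fixed classes of exactly m = 10 in the main calculation.

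**Step 1: reproduce the plan's figure.** Unpooled formula: n = (1.96 + 1.2816)² × (0.257×0.743 + 0.15×0.85) / 0.107² = 10.507 × (0.19095 + 0.12750) / 0.011449 = 292.3, so 293 per group. The pooled formula gives 296. Dropout: 293/0.8 = 366.25, so 367. The stated figures reproduce with a design effect of 1, so they contain no allowance for clustering. Power at 293 per group is 90.1% (unpooled) or 89.8% (pooled).

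**Step 2: design effect, exercise arm only.** DE = 1 + (m − 1) × ICC. With m = 10 and ICC 0.05, DE = 1 + 9×0.05 = 1.45. The control arm keeps DE = 1.

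**Step 3: actual error rate of the chi-square test.** When the average effect is zero but class effects vary, the true variance of the difference is (1 + DE)/2 times the one the test assumes. The error rate is 2 × [1 − Φ(1.96/√((1 + DE)/2))]. At ICC 0.05: (1 + 1.45)/2 = 1.225; 1.96/√1.225 = 1.771; error 7.7%.

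**Step 4: power of a test that allows for the clustering.** Unpooled: SE = √[(0.19095 + 0.12750×DE)/293]. At ICC 0.05: SE = √(0.37583/293) = 0.0358; 0.107/0.0358 − 1.96 = 1.03; power 84.8%. Using the pooled null variance instead gives 83.5%.

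| ICC (fixed classes of 10) | DE | Error of planned test | Power, clustered test (pooled – unpooled) |
|---|---|---|---|
| 0 | 1.00 | 5.0% | 89.8 – 90.1% |
| 0.01 | 1.09 | 5.5% | 88.5 – 89.0% |
| 0.02 | 1.18 | about 6.1% | 87.3 – 88.0% |
| 0.05 | 1.45 | 7.7% | 83.5 – 84.8% |

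**Step 5: smaller classes and shifting membership.** With classes of 5 at ICC 0.05, DE = 1.20, error 6.2%, power 87.0–87.8%. If a woman's class effect instead averages over 12 weekly classes with unrelated membership, DE = 1 + 9×0.05/12 = 1.0375. Then (1 + 1.0375)/2 = 1.01875, 1.96/√1.01875 = 1.942, and the error rate is 5.2%; power is 89.3–89.6%. Full mixing is one extreme and fixed classes the other.

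**The case against.** The strongest reply is that the classes are not clusters in the usual sense. Section 2.5 assigns women to sessions by gestation week, splits sessions according to numbers, lets absentees catch up later and runs a class even for one woman. Ten is therefore a cap, and no fixed class is described. This stands, and it makes 7.7% error with 84–85% power an upper case at ICC 0.05. Women at similar gestation may still move through the sessions together, so full mixing is not assured either.

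Second, the live class is a small part of the programme. At 20 minutes of home training a day (140 a week) plus two postural sessions of about 30 minutes, one of them live, class time is about 30 of 200 minutes a week, or 15%. The outcome is measured six weeks after delivery, when the classes have ended. This also stands, and argues for a low ICC.

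Third, a reader might infer that the planned test exceeds 5% under any null. It does not. Because randomisation is individual, chi-square keeps its level if the programme affects no woman. Inflation requires class or physiotherapist effects that vary around a zero average.

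Fourth, a reader might infer a much larger effect by treating the physiotherapist as the cluster, for example 293 women over ten centres, about 29 each. The protocol gives neither the number of physiotherapists nor a statement that classes run by centre, so that size has no basis.

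Finally, this is a condensed article, and a supporting analysis of therapist effects could sit in an analysis plan not shown. That does not answer the point in full, because the primary test and the power are both stated here without the condition they depend on.

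**Conclusion.** The point holds conditionally. The delivery in 2.5 creates possible clustering in one arm, and neither 2.8 nor the primary test in 2.9 allows for it. Any positive class or physiotherapist correlation makes the chi-square standard error too small and puts the power of a matching test below its value under independence. At ICC 0.01 to 0.02 the effect is small even with fixed classes of 10: at most about one percentage point on the error rate and two to three on power. The ICC 0.05 row is an upper case and should not be read as the trial's likely performance. All of this rests on an assumed ICC and class structure; at ICC 0 nothing changes. It is not an arithmetic error, since the sample size reproduces as stated. It merits a change because the remedy is cheap and the class and physiotherapist data must be captured while the classes run: 2.5 says no video or audio record is kept.

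**What to change.** **Data (2.5/2.6).** Add a class identifier and a physiotherapist identifier to the attendance record that site assistants already keep.

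**Analysis (2.9).** Report the EG–CG difference in six-week SUI with a variance that allows clustering in the exercise arm only. Use either a cluster-robust variance with a small-sample degrees-of-freedom correction or a partially nested model. Apply it within each imputed dataset before combining. Fix one cluster unit in advance, preferably the physiotherapist to whom each woman is first assigned or scheduled. The class attended most often is a poorer choice: it depends on attendance after randomisation and is ill-defined when women change sessions. Each control is her own cluster. If chi-square stays primary, make this a prespecified supporting analysis.

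**Sample size (2.8).** State that 90% power assumes no correlation within class or physiotherapist, and give the power over the assumed ICC range, for example the rows in the table above.

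**Cost.** Two fields on an existing record, a cluster rule written in advance and some analysis wording. The interval becomes slightly wider: at 25.7% against 15%, the standard error rises by about 2% at ICC 0.01 (0.0336 against 0.0330) and 9% at ICC 0.05 (0.0358 against 0.0330). The stated power becomes slightly lower. If there are few physiotherapists, the degrees of freedom will be small, so their number should be checked before the unit is fixed. No extra enrolment is proposed, which means accepting the lower power; restoring 90% at the pooled formula would take 308 analysed per arm at ICC 0.01 and 357 at ICC 0.05.

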## 2. Materials and Methods

### 2.1. Study Overview

The study is designed as a two-arm, parallel, RCT designed following the Consolidated Standards of Reporting Trials (CONSORT). Participants will be recruited from the obstetrics departments of ten hospitals (the centers) including Peking University People’s Hospital, Peking University International Hospital, Peking University Shenzhen Hospital, Beijing Obstetrics and Gynecology Hospital, Fangshan Maternal and Child Health Hospital of Beijing, Fengtai Maternal and Child Health Hospital of Beijing, Mentougou District Hospital of Beijing, Zhengzhou Central Hospital Affiliated to Zhengzhou University, Luohe Central Hospital of Henan Province and The First Obstetrics Hospital of Shanghai. The ten hospitals are selected as the centers because (1) they have enough patients to recruit the minimum number of patients proposed for each center, and (2) the investigators at those centers are knowledgeable and experienced in the identification and treatment of the SUI. 

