### 2.4. Randomization and Allocation Concealment

A randomization list will be created by a statistician from Peking University for each center before the start of the research using SAS 9.4 (SAS Institute, Cary, NC, USA). The numbers of participants in EG and CG are balanced, with a 1:1 ratio, and put into blocks of four. A unique study ID will be given to each participant. 

The randomization result for EG and CG are sealed in the ID-matching envelopes. The grouping details will be concealed to the investigators who will account for group allocation, recruitment, informed consent, and data collection. Eligible women are informed of grouping allocation via opening the sealed envelope after signing the informed consent. It is not feasible to blind to participants, urogynecologists and physiotherapists engaging in the intervention. However, all the investigators to perform patient evaluation and data analysis will be masked.

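### Randomisation is stratified by ten centres, but the primary test is an unadjusted chi-square or Fisher test, which is mildly conservative and fits poorly with multiple imputation

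*Protocol article*

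**What the plan says.** Four statements in the protocol article bear on this.

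- **Setting (2.1).** "Participants will be recruited from the obstetrics departments of ten hospitals".
- **Allocation (2.4).** "A randomization list will be created by a statistician from Peking University for each center before the start of the research", and "The numbers of participants in EG and CG are balanced, with a 1:1 ratio, and put into blocks of four". Randomisation is therefore stratified by centre.
- **Primary analysis (2.9).** "we will compare the occurrence of SUI at 6-week postpartum between EG and CG by chi-square test", or Fisher's exact test where that is appropriate. No centre term, effect measure or confidence interval is named for this outcome. Regression is named for the secondary outcomes only.
- **Missing data (2.9).** "The outcome analysis will be conducted with multiple imputations to take missing values into account". The only other approaches are "sensitivity analyses of the outcome first by imputing missing values as failures and then by using complete cases", so multiple imputation is the main analysis.

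**The concern.** Two choices made in 2.9 do not match the rest of the design.

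1. **Centre.** Balancing the arms within each centre removes between-centre variation from the treatment comparison. A test that pools all women puts that variation back into its standard error. If SUI rates differ between centres, the standard error is too large, the true type I error falls below 5%, and some power is given away.

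2. **Imputation.** Multiple imputation produces several completed 2×2 tables. Rubin's rules combine an estimate and its standard error from each. Fisher's exact test provides neither. The chi-square gives one p-value per table, and the plan names no effect measure to pool in its place. Nor does the plan as written lead to a risk difference with a confidence interval, although section 2.8 sizes the trial on a risk difference of 10.7 points.

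At stake are a little efficiency in the primary test and a clear route from the imputed datasets to one reported result.

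**Working it through.** **Inputs.** From 2.8: 25.7% (control) and 15% (exercise), two-sided 0.05, 90% power, 293 per group evaluable, 20% dropout, 367 per group recruited. From 2.1 and 2.4: ten centres, 1:1 within centre. Assumed, because the documents do not give it: between-centre SD of SUI on the logit scale, taken from 0 to 1.0.

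**Step 1: reproduce the plan's sample size.** With unpooled variance,

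n = [0.257×0.743 + 0.15×0.85] × (1.960 + 1.282)² / 0.107² = 0.3185 × 10.507 / 0.01145 = 292.3, so 293 per group.

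293 / 0.8 = 366.25, so 367 per group and 734 in total. Both stated figures reproduce. They are for the unadjusted comparison.

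**Step 2: effect of ignoring centre.** Simulation with 20,000 runs per scenario, ten near-equal centres, 293 per arm, balanced within centre. Centre effects are normal on the logit scale, and the intercept and treatment effect are set so that the overall rates stay at 25.7% and 15%. Pearson's chi-square is compared with the Cochran-Mantel-Haenszel (CMH) test stratified by centre.

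| Centre SD (logit) | 5th–95th percentile of centre control rates | Type I, chi-square | Type I, CMH | Power, chi-square | Power, CMH |
|---|---|---|---|---|---|
| 0 | 25.7% | 5.0% | 5.0% | 89.7% | 89.7% |
| 0.25 | 18–34% | 5.0% | 5.1% | 90.2% | 90.3% |
| 0.5 | 13–43% | 4.6% | 5.0% | 90.4% | 90.9% |
| 0.75 | 8–51% | 4.2% | 5.0% | 90.6% | 91.7% |
| 1.0 | 5–59% | 3.5% | 5.1% | 90.8% | 92.6% |

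A second simulation with calibrated rates gave 3.3% for the chi-square type I error at SD 1.0. The power difference is 0 at SD 0, about 0.5 point at SD 0.5, and 92.6 − 90.8 = 1.8 points at SD 1.0.

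Calibration matters. If centre effects with SD 1.0 are added without resetting the intercept, the overall rates drift to about 29% and 19%. The apparent power loss is then 87.8 − 84.6 = 3.2 points, but that no longer describes this trial's planned rates.

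**Step 3: imputation.** Suppose the imputed outcomes were analysed as if observed. With 20% missing, 587 of 734 outcomes are real, and the standard error used would be too small by the factor √(587/734) = 0.894. The effective critical value is 1.96 × 0.894 = 1.753, and the two-sided tail is 0.080. With 10% missing, √0.9 = 0.949, 1.96 × 0.949 = 1.859, and the tail is 0.063.

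As a check on the remedy, I simulated 367 per arm with 293 observed, 25.7% in both arms, outcomes missing completely at random and 20 imputations within arm. The risk difference pooled by Rubin's rules rejected in 5.1% of 20,000 runs, so proper pooling restores the nominal level.

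**The case against.** - **The centre effect is small and on the safe side.** This stands. The unadjusted test does not produce extra false positives, its planned power stays at about 90%, and it matches the test for which the trial was sized. The size of the loss also rests on a between-centre spread that the documents do not give.
- **Pooling is detail for the analysis plan.** This largely stands. The article condenses a fuller protocol, and the analysis plan is not shown. Chi-square statistics can be combined across imputations by a special rule, and each imputed 2×2 table yields a risk difference with a standard error. The absence of a combining rule or of an imputation model is therefore no fault in itself. What remains is that the article positively names tests that do not lead naturally to a pooled estimate.
- **Fisher's test would hardly be used.** At the planned rates the smallest expected cell is 293 × (0.257 + 0.15) / 2 ≈ 60, so the chi-square would apply. This stands, and it narrows the Fisher point to one of wording.
- **A stronger reading that the text does not support.** A reader might infer that the primary test will run at about 8% type I error. That needs imputed values to be treated as observed, and all 20% dropout to be missing at week 6. The article says neither. It specifies multiple imputation, whose purpose is to carry the uncertainty of imputation, and the 20% is a general dropout allowance in a trial with follow-up to 12 months.

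**Conclusion.** The point holds in a limited form. The primary test ignores the centres within which women are randomised. If SUI rates vary between centres, it is mildly conservative: type I error falls from about 5.0% to 3.3–3.5%, and power loss is 0 to about 2 points, over an assumed logit SD of 0 to 1.0. At a moderate SD of 0.5 the figures are 4.6% and about 0.5 point. These results assume ten near-equal centres and the rates in 2.8. The sample size does not change.

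The mismatch with multiple imputation is real but secondary: the main analysis is imputed, while the named tests come without an effect measure to pool. The figure of about 8% is what a faulty implementation would cost, not what the plan prescribes.

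This should be fixed because the change is nearly free. It does not threaten the validity of the trial.

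**What to change.** In 2.9, replace the primary test by one of two analyses:

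- a Mantel-Haenszel risk difference stratified by centre; or
- a logistic regression of 6-week SUI on arm and centre, standardised to a risk difference. The standardisation step needs stating, because the model itself gives an odds ratio.

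State that the chosen estimate and its standard error are obtained in each imputed dataset, pooled by Rubin's rules, and reported as a risk difference with a 95% CI. Keep the chi-square as an unadjusted check on complete cases, which 2.9 already plans as a sensitivity analysis.

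The cost is a change of wording and slightly more programming. It needs no extra data, visits or participants. It should be settled before anyone sees outcomes by arm.
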